### Design

This feasibility pilot study is a multisite, 2-armed cluster RCT taking place in work organizations of different sizes and sectors across the Midlands area of England. The organizations are the units of randomization (the clusters), with data collected from individual line managers (the participants) and the direct reports who are supervised by managers within those organizations. If large, multisite organizations are recruited for the study, we will consider the option of using an internal control group within that organization if there is a low risk of contamination between the intervention arm and control arm within that large organization. The data collection schedule for the study is summarized below for the intervention arm (Table 2) and the control arm (Table 3). A repeated measures design will be adopted, whereby participating line managers in the intervention arm will complete web-based questionnaires at baseline, on completion of the MMW training (approximately 6 weeks after baseline), and at 3- and 6-month follow-up periods after baseline. A 3-month waitlist control group will be used with participating line managers. They will be asked to complete web-based questionnaires at baseline, 3-month follow-up (before starting the intervention), and after completion of the training (6 months after baseline).

**Table 2 table2:** Data collection schedule for the intervention arm.

			Baseline survey		Postintervention survey (approximately 6 weeks after baseline)		3 months after the baseline follow-up survey		6 months after the baseline follow-up survey		Process evaluation interviews

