### Sample Size

A minimum of 8 clusters (randomized into 2 groups of 4) will be sought to inform a future trial, as recommended for pilot clinical trials [26]. We will aim to recruit 30 line managers for each arm as per guidance for feasibility trials [27].

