### Allocation to Intervention

Organizations (clusters) will be randomly assigned (1:1) to either the intervention or waiting list control group using a web-based random sequence generator [28]. This allocation will be stratified to ensure a spread of different sizes of organizations within the intervention and control arms. Where the organization is sufficiently large to have distinct departments, divisions, or units with minimal risk of contamination between them, we will randomly assign 2 of these different departments, divisions, or units to either intervention or waiting list control using the same approach.

The research team and participants will not be blinded to the outcome of randomization due to practical reasons (ie, sending reminder emails to participating managers). The lead researcher will enroll participating organizations and line managers and will assign organizations (clusters) to the intervention or control arm.

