### Measures for Direct Reports (Intervention and Control)

#### Overview

On registering for the training, all participating line managers in both the intervention and control arms will be asked to send an invitation to participate in a web-based survey to their direct reports. The purpose of this is to assess whether completion of the training by line managers affects their direct reports’ perception of line managers’ behavior or the mental health and sickness absence outcomes of direct reports. The web-based survey for direct reports will contain the following items: demographics (age, gender, and number of years in the organization) collected at baseline only, WEMWBS 14-item [25], SMCIT-employee version [13], and a single-item self-reported productivity rating.

The web-based survey for direct reports at follow-up will contain the same items (as above) with the addition of open-response questions about any changes to how they are managed or their line manager’s behavior.

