### Data Analysis

Statistical analysis will produce summary statistics to assess the parameters for a full trial. Missing data will be imputed using multiple imputations. SPSS (version 26; IBM Corp) will be used for statistical analysis. As this is a pilot trial, no emphasis will be put on the *P* values for any inferential statistical tests conducted. The primary analysis will use an intent-to-treat approach with repeated measures. Differences between the intervention and waiting list control groups at follow-up will be examined against baseline. The pilot data will provide information on the parameters needed for a realistic sample size calculation (mean, SD, and treatment effects of the primary outcome for the 2 arms) for a future main cluster RCT.

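### The stated primary analysis of this cluster-randomised pilot names no term for the randomised unit, none for manager among direct reports, and no ICC among the parameters to be estimated

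*Protocol article*

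**What the plan says.** The Design section of the protocol article sets the levels: "The organizations are the units of randomization (the clusters), with data collected from individual line managers (the participants) and the direct reports". Under Allocation to Intervention, "Organizations (clusters) will be randomly assigned (1:1) to either the intervention or waiting list control group". For a sufficiently large organisation, "we will randomly assign 2 of these different departments, divisions, or units to either intervention or waiting list control". The randomised unit is therefore usually the organisation and sometimes a part of one.

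Direct reports add a further level. They are reached through their own manager: "all participating line managers in both the intervention and control arms will be asked to send an invitation" (Measures for Direct Reports, Overview). Several of them may complete the employee version of the competency tool about the same manager.

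On analysis, the Data Analysis section says: "The primary analysis will use an intent-to-treat approach with repeated measures". It adds that the arms are compared at follow-up against baseline, that missing data are multiply imputed, that SPSS is used, and that P values carry no emphasis. The quantities it lists for sizing the future cluster trial are means, SDs and treatment effects by arm. The Objectives section, however, makes parameters on both sample size and clustering an objective (numbered 3a under Outcome Measures).

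**The concern.** Managers in one organisation share an employer, a gatekeeper and a workload climate. Direct reports of one manager share that manager as well. When whole organisations are allocated, this shared variation enters the difference between arms and has to enter its standard error. The only dependence that the analysis sentence recognises is between repeated measurements on one person.

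The omission of the ICC from the parameter list points the same way. A model with a term for the randomised unit would yield the between-cluster variance directly, and objective 3a needs it, yet it is not among the stated outputs.

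Two things are at stake. The apparent potential for improving manager and direct-report outcomes could look firmer than the data allow. The main cluster trial could also be planned without the quantity that drives its size.

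**Working it through.** **No figure to reproduce.** The protocol gives no ICC, power, effect size or planned interval. The check asks how far a standard error that ignores the clusters would fall short.

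**Inputs from the protocol**
- Sample Size: "A minimum of 8 clusters (randomized into 2 groups of 4) will be sought to inform a future trial", and "We will aim to recruit 30 line managers for each arm". That is 60 managers in 8 clusters, so 60/8 = 7.5 per cluster.
- Results: 224 managers in 24 organisations, so m = 224/24 = 9.33. This takes each organisation as one randomised unit; the article does not say how many were split.
- Outcome Measures: retention targets of 70% at 3 months and 50% at 6 months.
- Recruitment: each manager supervises at least 3 staff. The number who respond is not given.

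**Assumptions**
- ICC of the baseline-adjusted or change score: 0.01 to 0.10.
- Coefficient of variation (CV) of cluster size: 0 or 0.8.
- Direct reports: r = 3 responders per manager, same-manager correlation 0.05 to 0.30, and correlation between reports of different managers in one organisation 0.01 to 0.05.

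**Managers, equal clusters.** Design effect DE = 1 + (m − 1) × ICC. The correct standard error is √DE times the unadjusted one. Coverage of an unadjusted 95% interval is 2Φ(1.96/√DE) − 1.

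| ICC | DE, m = 7.5 | SE factor | Coverage | DE, m = 9.33 | SE factor | Coverage |
|---|---|---|---|---|---|---|
| 0 | 1.00 | 1.00 | 95.0% | 1.00 | 1.00 | 95.0% |
| 0.01 | 1.07 | 1.03 | 94.2% | 1.08 | 1.04 | 94.0% |
| 0.02 | 1.13 | 1.06 | 93.5% | 1.17 | 1.08 | 93.0% |
| 0.05 | 1.33 | 1.15 | 91.1% | 1.42 | 1.19 | 90.0% |
| 0.10 | 1.65 | 1.28 | 87.3% | 1.83 | 1.35 | 85.2% |

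**Managers, unequal clusters.** DE = 1 + ((1 + CV²)m − 1) × ICC. With CV = 0.8 and m = 9.33, (1 + CV²)m = 1.64 × 9.33 = 15.31.
- ICC 0.01: DE 1.14, SE factor 1.07.
- ICC 0.05: DE 1.72, SE factor 1.31.
- ICC 0.10: DE = 1 + 14.31 × 0.10 = 2.43, SE factor 1.56.

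**After attrition, equal clusters.** At 70% retention, m = 6.53. DE is 1.28 at ICC 0.05 (SE factor 1.13) and 1.55 at ICC 0.10 (factor 1.25). At 50%, m = 4.67 and DE at ICC 0.05 is 1.18 (factor 1.09).

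**Direct reports.** DE = 1 + (r − 1)ρ_manager + r(m − 1)ρ_org, with r = 3 and m = 9.33, so r(m − 1) = 25.
- ρ_manager 0.05, ρ_org 0.01: 1 + 0.10 + 0.25 = 1.35, SE factor 1.16.
- 0.10 and 0.02: 1 + 0.20 + 0.50 = 1.70, SE factor 1.30.
- 0.15 and 0.05: 1 + 0.30 + 1.25 = 2.55, SE factor 1.60.
- 0.30 and 0.05: 1 + 0.60 + 1.25 = 2.85, SE factor 1.69.

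**Degrees of freedom.** Even at ICC = 0, a cluster-level t interval at the planned 8 clusters has 6 degrees of freedom and is 1.22 times as wide as one on 58. At 24 clusters (22 against 222 degrees of freedom) the ratio is 1.05.

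**Split organisations.** If two departments of one organisation go to opposite arms, the effect they share cancels in the contrast. Leaving it out of the model then makes the standard error too large for that component. Effects specific to each department still act in the usual direction.

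**The case against.** The best defence is that the analysis sentence is brief, not wrong. It gives no unit of analysis, model family or covariance structure. A mixed model with organisation as a random effect is also a repeated-measures analysis. The design plainly recognises clustering, and a condensed article may leave random effects and degrees of freedom to an analysis plan that is not shown. This stands to the extent that the protocol nowhere says managers will be treated as independent. It does not remove the point. The article chose to state its primary analysis and its target parameters, and the parameter list leaves out the ICC that objective 3a needs.

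A reader might go further and infer that every effect interval will be too narrow. The documents do not support that. No interval is named, the size depends on an ICC that is not given, the shortfall is only about 3% to 4% in standard error at ICC 0.01, and split organisations can reverse the direction. Nor do they support a claim that intervals for retention are understated: retention is reported as percentages against targets, with no interval planned, and the analysis sentence is not about retention.

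It is also fair that the direct-report range is soft. Well-being, productivity and absence are not ratings of the manager, so the higher same-manager correlations are less plausible for them.

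**Conclusion.** The point holds in a limited form. The stated analysis does not carry the randomised unit or the manager level, and the stated outputs omit the ICC that the protocol's own objective calls for. If the analysis is run as written and the ICC is positive, manager-level standard errors should be about 1.04 to 1.35 times larger (ICC 0.01 to 0.10, equal clusters of 9.33), up to 1.56 times at CV 0.8, and less after attrition. For direct reports the factor is about 1.16 to 1.69. These sizes rest wholly on assumed correlations, cluster-size variation and responders per manager, and on organisations not being split between arms.

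The importance is moderate. This is a feasibility pilot that puts no emphasis on P values, and its declared benchmarks (8 organisations, 70% and 50% retention) do not depend on a treatment-effect interval. The main loss is to objective 3a and to how firmly the effect estimates can be read.

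**What to change.** In the Data Analysis section, state the primary analysis as a linear mixed model for the repeated measures with:
- a random effect for the randomised unit, plus one for organisation where an organisation is split between arms;
- a manager random effect for direct-report outcomes;
- Satterthwaite or Kenward-Roger degrees of freedom.

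A t test on cluster summaries is an acceptable alternative. Add the ICC, with its interval, to the parameters to be reported for the main trial.

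The Results section says that analysis finished in August 2023 and that publication was still to come. The practical step is therefore to confirm which model was fitted and, if it had no cluster terms, to rerun it before reporting. No new data are needed. The cost is slightly more analysis work and generally wider intervals. The ICC interval will itself be wide with this few clusters, and the report should say so.

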### Economic Measures

We will consider the feasibility of collecting data on costs and savings from the perspective of the employer. The costs considered will be the working hours lost to complete training during working hours, and, in turn, the cost or saving of any change in sickness absence rate over the follow-up will be calculated based on the median hourly wage (£15.6 [US $19.87] per hour) [32] of employees in the United Kingdom.

### Process Evaluation

#### Overview

A qualitative process evaluation will run alongside the pilot trial to explore the experience of the intervention with line managers and other stakeholders (eg, human resource managers and well-being coordinators) within participating organizations; assess the acceptability, usability, and utility of the intervention; and identify barriers and facilitators to implementation. Semistructured interviews will be used to collect the data to inform the process evaluation. In addition, module feedback forms will be completed by line managers after each of the 5 modules in the training course to allow more specific feedback relating to each module, including any changes in their managerial practice that participants are planning to make as a result of completing each module.

For the process evaluation interview study, participants will be invited to take part in interviews after the 6-month follow-up. Interviews will take place with (1) line managers in the intervention arm and (2) stakeholders in both the intervention and control arms.

Interviews will be conducted face-to-face, by video call, or by telephone at the participant’s preference and arranged at a mutually convenient time and location. The interview schedule will cover the following research questions and topics: acceptability, usability, and utility of the intervention; changes the line manager has introduced since undertaking the training; barriers and facilitators to the intervention implementation and effectiveness; and suggested improvements to the intervention. The interviews with stakeholders will cover the following research questions and topics: barriers and facilitators to taking part in the study; acceptability of the waitlist control condition (control arm only); acceptability, usability, and utility of the intervention; and barriers and facilitators to the intervention implementation and effectiveness. For stakeholders, the gatekeeper for each participating organization (intervention and control arms) will be asked to email an invitation to participate in an interview to all relevant stakeholders within their organization (eg, human resource managers, well-being managers, learning and development managers, and trade union representatives). Principles of data saturation will be used to guide the final sample size, but as a guideline, we would expect there to be interviews with approximately 20 line managers and 1-2 stakeholders per participating organization. All interviews and analyses will be conducted by members of the research team (CB, BV, and LT). Interviews will be guided by the interview schedules and audio recorded where consent is given. Digital audio files will be transcribed and fully anonymized.

#### Data Analysis

The qualitative data collected will be analyzed using thematic analysis [33,34] guided by the principles of framework analysis [35,36]. The Consolidated Framework for Implementation Research [37] and the Technology Acceptance Model [38,39] will be used to provide overarching frameworks for the qualitative analysis.

### Study Management

The study management group will be the research team based at the University of Nottingham and Nottinghamshire Healthcare National Health Service Foundation Trust’s Institute of Mental Health. A wider advisory group will include researchers from other UK universities who are part of the wider MHPP team and who will meet monthly to monitor progress. All data will be managed according to the GDPR, anonymized as soon as possible, and kept securely on a database that can only be accessed by the research team.

The study duration will be 24 months, with participating organizations starting to be enrolled in June 2021, and the study will cease at the end of May 2023.

### Criteria for Terminating the Study

The study may be stopped as a result of a formal or informal interim analysis and based on overwhelming evidence of efficacy or inefficacy, major safety concerns, new information, or issues with study conduct (eg, poor recruitment and loss of resources). The study may be stopped at a single site as a result of a formal or informal interim analysis and based on major safety concerns at that site, new information, or issues with study conduct at that site (eg, poor recruitment and loss of resources).

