**Methods:**

We use a cluster randomized controlled trial design consisting of 2 arms, the intervention arm and a 3-month waitlist control, in this multicenter feasibility pilot study. Line managers in the intervention arm will complete a baseline questionnaire at screening, immediately post intervention (approximately 6 weeks after baseline), and at 3- and 6-month follow-ups. Line managers in the control arm will complete an initial baseline questionnaire, repeated after 3 months on the waitlist. They will then be granted access to the MMW intervention, following which they will complete the questionnaire post intervention. The direct reports of the line managers in both arms of the trial will also be invited to take part by completing questionnaires at baseline and follow-up. As a feasibility pilot study, a formal sample size is not required. A minimum of 8 clusters (randomized into 2 groups of 4) will be sought to inform a future trial from work organizations of different types and sectors.

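### The termination clause lets a feasibility pilot with no formal sample size stop for efficacy or inefficacy after an informal interim look, which conflicts with the study's stated purpose and inferential stance

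*Protocol article*

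**What the plan says.** The Criteria for Terminating the Study section has two sentences. The first covers the whole study: "The study may be stopped as a result of a formal or informal interim analysis and based on overwhelming evidence of efficacy or inefficacy". It then adds safety, new information and conduct as further grounds. The second covers a single site. It also mentions a formal or informal interim analysis, but its grounds are limited to a stop "based on major safety concerns at that site, new information, or issues with study conduct at that site". Efficacy is not among them.

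Other sections describe a study that is not set up for such a decision:

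- Abstract, Methods: "As a feasibility pilot study, a formal sample size is not required".
- Sample Size: "A minimum of 8 clusters (randomized into 2 groups of 4) will be sought to inform a future trial", and "We will aim to recruit 30 line managers for each arm as per guidance for feasibility trials".
- Data Analysis: "As this is a pilot trial, no emphasis will be put on the *P* values". The same section says that the pilot is to supply the mean, SD and treatment effects needed to size a main cluster trial.
- Allocation to Intervention: "The research team and participants will not be blinded to the outcome of randomization".
- Study Management: the research team is the study management group, and a wider advisory group meets monthly to monitor progress.
- Discussion: the authors expect no more than early signs of change in the outcomes.

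**The concern.** A study that gives its final P values no emphasis has no stated basis for acting on stronger inferential evidence at an earlier point with fewer data. The clause goes further and accepts an informal analysis as enough. The people best placed to make that informal look are unblinded, and they also enroll organizations, allocate them and send reminders.

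What is at stake is the pilot's own output. Several of its deliverables exist only if follow-up runs to month 6 or beyond. The treatment effect is to be carried into a main-trial sample size calculation, and an estimate taken at a data-driven stop is biased in the direction that triggered the stop.

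**Working it through.** **1. Is there a figure to reproduce?** No. The article gives no alpha, power, effect size, intracluster correlation (ICC), interim time or boundary. The planned size is simple arithmetic: 2 arms × 4 clusters = 8 clusters; 2 × 30 = 60 managers; 60/8 = 7.5 per cluster. The Results section reports 224 managers in 24 organizations, or 224/24 = 9.3 per cluster.

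**2. When could a between-arm look occur?** Tables 2 to 4 give the 6-week survey to the intervention arm only, so the first between-arm data come at month 3. Recruitment ran from September 2021 to January 2022. The first month-3 data would therefore arrive from about December 2021, near the close of recruitment, and the last around April 2022.

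**3. What would a stop at or after month 3 remove, and what would it leave?**

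| Deliverable (section) | When it is complete | After an efficacy or inefficacy stop |
|---|---|---|
| Employer conversion, manager recruitment (Trial Feasibility and Acceptability-Related Outcomes) | During recruitment | Largely kept |
| Baseline SD and baseline clustering (Data Analysis; Objectives) | Baseline | Largely kept |
| Retention, 70% at month 3 and 50% at month 6 (Trial Feasibility and Acceptability-Related Outcomes) | Month 6 | Month-6 part lost or cut short |
| Absence over the 6 months after completing the intervention (Organizational Sickness Absence Records) | After month 6 | Lost or cut short |
| Interviews (Process Evaluation) | After month 6 | Lost or cut short |
| Treatment effect for the main trial (Data Analysis) | Month 3 onward | Biased if the look uses partial month-3 data; later data lost |

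**4. How large could the bias be?** This is an illustration on assumed values, because the article supplies none. Assume a look when half of the planned managers have month-3 data (15 per arm), a true standardized effect d, and an ICC of 0 or 0.05.

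- Design effect: DE = 1 + (7.5 − 1) × ICC, which is 1 at ICC 0 and 1.325 at ICC 0.05.
- Effective n per arm: 15/DE = 15.0 or 11.3.
- Standard error of d: √(2/n_eff) = 0.365 or 0.420.
- Mean estimate given a stop for efficacy at z > b: d + SE × φ(b − d/SE) / [1 − Φ(b − d/SE)].

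| True d | Boundary b | Chance of stopping | Mean estimate if stopped | Ratio to truth |
|---|---|---|---|---|
| 0.3 | 1.96 | 11% to 13% | 0.90 to 1.03 | 3.0 to 3.4 |
| 0.3 | 3.0 | 1.1% to 1.5% | 1.22 to 1.41 | 4.1 to 4.7 |
| 0.5 | 1.96 | 22% to 28% | 0.94 to 1.07 | 1.9 to 2.1 |
| 0.5 | 3.0 | 3.5% to 5.1% | 1.25 to 1.43 | 2.5 to 2.9 |

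The stricter the boundary, the rarer the stop and the larger the exaggeration when it happens. A stop for inefficacy would bias the estimate the other way.

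**5. Does a false-positive rate follow?** No, because it depends wholly on the boundary assumed. In simulation with equally spaced looks, a nominal two-sided 5% test at every look gives 8.3% with 2 looks, 10.7% with 3 and 14.2% with 5. With an interim boundary of |z| > 3 and 1.96 at the end, the figures are 5.1%, 5.2% and 5.3%. The article describes neither rule, so neither set of figures measures its defect.

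**The case against.** The strongest case on the other side has five parts.

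- **The clause is permissive and sets a high bar.** It says the study may be stopped, and it asks for overwhelming evidence. At the planned size that bar could hardly be met: for 30 managers per arm and an ICC of 0 to 0.10, the effect detectable with 80% power is d = 0.72 to 0.93. This lowers the chance of harm but does not make the clause coherent.
- **Boundaries, timing and the decision body may be in a SAP or full protocol that is not shown.** That is right, and their absence is no part of this point. But no such document would remove the word informal or the conflict with the Data Analysis section.
- **Informal review is ordinary for recruitment, resources and safety.** This stands. The defect is confined to the efficacy/inefficacy ground, and the single-site sentence needs no change.
- **The team is not alone.** A wider advisory group monitors progress monthly. This stands as far as it goes; the article does not say whether that group is independent or decides on stopping.
- **No early stop is mentioned.** Recruitment passed its target and the analysis was finished in August 2023. This stands and limits the practical weight of the point.

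A reader might infer two stronger claims, and the article supports neither. The first is that a stop would destroy the pilot's parameters. Baseline SD, baseline clustering and recruitment figures do not depend on month-6 data, and a stop near the close of recruitment would leave them largely intact. The second is that a study of this size could never yield strong evidence. That fits the planned 60 managers. With the 224 recruited, assuming 112 per arm and an ICC of 0 to 0.10, power for d = 0.5 is 79% to 96%. The conflict therefore rests on the study's stated purpose and inferential stance, whatever its size.

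**Conclusion.** Wrong as written. The whole-study sentence allows a stop for efficacy or inefficacy that the rest of the article gives no basis for, and it lets an informal look by unblinded staff suffice. If used, it would cut off month-6 retention, post-intervention absence and the interviews. If the look used incomplete month-3 data, it would also bias the treatment effect intended for the main trial. The ratios of about 2 to 5 in the working show how large that bias could be, under an assumed look at half the planned size, d of 0.3 or 0.5 and an ICC of 0 or 0.05; they are not properties of the plan. A stop after month-3 data were complete would leave the month-3 estimate free of truncation and cost only the later follow-up.

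The actual effect on this study was probably small. That is an inference from the article's silence about any early stop, and does not show that no look took place.

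**What to change.** 1. In the whole-study sentence of Criteria for Terminating the Study, delete the efficacy/inefficacy ground.
2. Add one sentence: no between-arm comparison of the effectiveness outcomes will be used to stop the study before the 6-month data are complete.
3. Keep safety, new information and conduct as they stand. Retention should still be monitored by arm, as the feasibility outcomes require; pooling it would hide differential drop-out.
4. Leave the single-site sentence unchanged.
5. As the study is complete, state in the results report whether any interim between-arm look at outcomes took place and, if so, when and by whom. Do not carry the clause into the main-trial protocol without a prespecified rule.

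The cost is one deleted phrase, one added sentence and one line of reporting. No planned analysis is lost and no sample size changes.
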